## **5.2 Use of co-intervention (if applicable)**

Not applicable.

## **5.3 Escape medication (if applicable)**

Not applicable.

## **6. INVESTIGATIONAL PRODUCT**

Not applicable. The treatment (i.e., nutritional prehabilitation as described in paragraph 5.1) used in this study is part of standard clinical care, applied to patients with head and neck cancer with high risk of malnutrition based on the MUST. The execution of nutritional prehabilitation is in accordance with our current standard clinical practice, in line with local, national and worldwide guidelines.

## **7. NON-INVESTIGATIONAL PRODUCT**

Not applicable. No medicinal products, food products, chemical compounds, stable isotopes or other products are used in an experimental setting. All dietary interventions are administered in compliance with our current standard clinical practice, in line with local, national and worldwide guidelines.

## 8. METHODS

### 8.1 Study parameters/endpoints

#### 8.1.1 Main study parameter/endpoint

The primary outcome will be adverse events (intra- and postoperative complications and (chemo)radiotherapy toxicity). Relevant complications include hemorrhage, infection and wound healing disorders including dehiscence and fistula.

Complications will be measured within 30 days after surgery using the Clavien-Dindo classification and evaluated during hospital stay and planned and unplanned outpatient visits [22]. Clavien-Dindo grade  $\geq 2$  complications will be deemed clinically relevant. Toxicity will be evaluated using the Common Terminology Criteria for Adverse Events (CTCAE), version 4.0, at 6 and 12 weeks after the start of (chemo)radiotherapy [23]. The following domains are scored within the CTCAE: xerostomia, taste, throat pain, oral pain, general pain, dysphagia, hoarseness and mucositis. Clinically relevant toxicity will be defined as CTCAE toxicity grade  $\geq 3$ , irrespective of the mentioned domains.

Both complications and (chemo)radiotherapy toxicity are evaluated as part of our current standard practice.

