### **4.3 Exclusion criteria**

A potential subject who meets any of the following criteria will be excluded from participation in this study:

- Previous surgical or radiotherapeutic treatment of the neck;
- Multiple simultaneous primary malignancies;
- Disability that could interfere with questionnaire fulfillment.

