Dietetic consultations will be scheduled biweekly. Depending on the patients' needs and preferences, the frequency of consultations may be increased, e.g., in case of weight loss or inability to use oral intake. These consultations may take place in-person at the outpatient department or through video or telephone calls. The first consultation takes on average 30 minutes, follow-up consultations on average 15 minutes. We expect that in 10-20% of included patients dietary advice in the form of an energy and protein enriched diet will be sufficient and 80-90% of patients will be offered oral nutritional supplements to meet estimated nutritional requirements. Patients rarely need enteral nutritional support in this prehabilitation stage.

Nutritional prehabilitation will start as soon as patients are included in the study, which is within one week after their first visit to the outpatient department, depending on the time needed to consider participation in the trial. The expected variation in duration of the intervention is three to four-and-a-half weeks. The **prehabilitation** intervention ends as

soon as treatment for their head and neck cancer commences. Patients will still be receiving nutritional care as is standard care (i.e., postoperatively and/or during (chemo)radiotherapy). Nutritional care given during treatment is the same as nutritional care that is outlined in this paragraph (i.e., given as a prehabilitation intervention). Patients undergoing (chemo)radiotherapy are all counseled by a dietitian during their treatment. Patients undergoing surgery will receive nutritional care as indicated by their MUST score or as indicated by the “Perioperatief voedingsbeleid” guideline: inability to start oral intake within 48 hours after surgery or no more than 50% of the recommended daily energy intake on the fifth day postoperatively [21].

Patients enrolled in the control arm of the study will receive standard care, which means they will not receive any nutritional counseling or nutritional intervention before treatment commences.

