#### 8.1.2 Secondary study parameters/endpoints

Secondary outcome measures will be patient-reported quality of life outcome measures (i.e., the EAT-10, EORTC H&N35 and EORTC C30 questionnaires), recurrence and (disease-specific and overall) survival. Patients will be monitored for two years with intervals of at least three months. These intervals coincide with regular follow-up visits to the outpatient departments. The questionnaires will be fulfilled at baseline and at 3, 6, 12, 18 and 24 months after last treatment. Lastly, the EQ-5D-5L, *i*MCQ and *i*PCQ will be administered to be able to perform a cost-utility and cost-effectiveness evaluation. The EQ-5D-5L, *i*MCQ and *i*PCQ will be fulfilled in the first year of follow-up at baseline and at 3, 6 and 12 months after last treatment. The EORTC H&N35, EORTC C30, EQ-5D-5L questionnaires are part of our current standard practice, as well as the evaluation of recurrence and survival. The EAT-10, *i*MCQ and *i*PCQ are not part of our current standard practice.

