#### 8.1.3 Other study parameters

Baseline characteristics include age, gender, smoking status, alcohol use, tumor site, tumor stage, (intended) type of treatment, length, weight (loss), skeletal muscle mass, number of dietetic consultations, dietary intake using 24-hour recall, nutritional status

using the MUST, Global Leadership Initiative on Malnutrition (GLIM)-criteria, Patient Generated Subjective Global Assessment Short Form (PG-SGA SF) score and bio-electrical impedance analyses (BIA)-measurements, physical status using grip strength and Timed Up and Go Test (TUG), and skeletal muscle mass. Dietary intake using 24-hour recall, GLIM-criteria, PG-SGA SF and BIA-measurements will not only be performed at baseline to assess nutritional status, but also at the end of the dietetic intervention (or, for the control group, just before the treatment starts), and three months after the final treatment.

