## **8.3 Study procedures**

*Procedures that are part of standard clinical practice:*

- Diagnostic head and neck CT scans, which will be used to measure pre-treatment CSMA at the level of C3 [29, 30, 32]. The acquired CSMA at the level of C3 will be converted to CSMA at the level of L3 and subsequently corrected for patients' squared height to obtain the LSMI. Low LSMI will be defined as lower than 46.5 cm^2/m^2 for men and lower than 37.9 cm^2/m^2 for women [13];
- Intra- and postoperative complications measured within 30 days after surgery using the Clavien-Dindo classification;

- (Chemo)radiotherapy toxicity measured 6 and 12 weeks after the start of (chemo)radiotherapy using the CTCAE version 4.0;
- EORTC H&N35 measured for two years at baseline and at 3, 6, 12, 18 and 24 months;
- EORTC C30 measured for two years at baseline and at 3, 6, 12, 18 and 24 months;
- EQ-5D-5L measured at baseline and at 3, 6, 12, 18 and 24 months.

*Procedures that are not part of standard clinical practice and all of which will not postpone diagnostic procedures or treatment:*

- Grip strength, which will be measured using a Jamar hydraulic handheld dynamometer as recommended by the American Society of Hand Therapists and expressed in kilograms. Patients will be asked to squeeze maximally with each hand. Each hand will be measured three times. Low grip strength will be defined as lower than 27 kg in men and lower than 16 kg in women [25]. This measurement will be performed at baseline and takes less than five minutes to complete;
- BIA-measurements to estimate body composition, including body fat and muscle mass, using a weak electric current that flows through the body. The measurement will be performed at baseline, just before the treatment starts, and three months after the final treatment. It takes on average 15 minutes to complete;
- EAT-10 in the first two years of follow-up at baseline and at 3, 6, 12, 18 and 24 months after last treatment. The EAT-10 consists of 10 questions in three domains: functional, emotional and physical. Time to complete the EAT-10 is on average two minutes;
- iMCQ in the first year of follow-up at baseline and at 3, 6 and 12 months after last treatment. The iMCQ consists of 20 questions. Time to complete the iMCQ is on average 10 minutes;

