#### **11.4.1 Risk assessment**

There is extensive experience with the dietary measures as outlined in 5.1. They are based on local, national and worldwide protocols and guidelines on nutritional support for (head and neck) cancer patients. All patients with high risk of malnutrition based on the

MUST receive dietary measures. Patients with high risk of malnutrition are frailer and more frequently experience swallowing problems than the study population. The study population is a low-risk patient group compared to the patient group already receiving the intervention.

Oral nutritional supplements (e.g., nutridrinks) and enteral nutritional support used in this study comply with the FDA regulations regarding ingredients, labelling and manufacturing process.

Common potential adverse events/risks of the use of oral nutritional supplements are excessive mucus formation. The use of oral nutritional supplements is not expected to increase swallowing difficulties. Common potential adverse events/risk of the use of enteral nutritional support are nausea, vomiting, diarrhoea, constipation, irritation of the nose of throat, a blocked feeding tube needing replacement. Adverse events will be monitored during consultations with the dietitian and medical specialists.

Given the extensive experience with the intervention in a patient population that is high-risk compared to the study population and the small change of adverse events that cause slight damage at most, we think this study can be considered a negligible-risk study.

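### The primary toxicity endpoint uses an absolute CTCAE grade with no pre-treatment grade, so severe tumour symptoms already present at entry count as events in both arms and dilute the contrast

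*Protocol*

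**What the plan says.** Section 8.1.1 lists the toxicity items: "The following domains are scored within the CTCAE: xerostomia, taste, throat pain, oral pain, general pain, dysphagia, hoarseness and mucositis". It then sets the event: "Clinically relevant toxicity will be defined as CTCAE toxicity grade" 3 or higher, in any of these domains. Section 10.1 repeats the definition. Section 8.3 gives the timing: "Chemo)radiotherapy toxicity measured 6 and 12 weeks after the start of (chemo)radiotherapy using the CTCAE version 4.0". The Summary and section 8.5 name 6 weeks only; that difference does not affect this point.

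The baseline list in section 8.1.3 begins "Baseline characteristics include age, gender, smoking status, alcohol use, tumor site, tumor stage, (intended) type of treatment" and goes on to nutritional and physical measures. It contains no CTCAE grade. Nowhere does the protocol require a change from baseline or a judgement that the symptom was caused by treatment.

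Patient-reported symptoms are collected before treatment. For EAT-10, EORTC H&N35 and EORTC C30, section 8.1.2 says: "The questionnaires will be fulfilled at baseline and at 3, 6, 12, 18 and 24 months after last treatment". Nothing links these scores to the primary endpoint. Section 10.1 foresees adjusted logistic regression only if the arms turn out unbalanced.

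**The concern.** The trial enrols stage III and IV carcinoma of the oral cavity, oropharynx, hypopharynx or larynx (section 4.2). Throat pain, oral pain, general pain, dysphagia and hoarseness can be symptoms of the untreated tumour at these sites. Entry is restricted by MUST score, which concerns malnutrition risk and not pain or voice.

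A patient who enters with a grade 3 symptom in one domain and still has it at 6 weeks is a toxicity event by definition, even if radiotherapy added nothing. Prehabilitation starts after enrolment and cannot prevent that event. Such events should occur about equally often in both arms. They raise both event rates, narrow the difference and lower the power of the primary test. An assessment that was never scheduled cannot be recovered at the analysis stage: once treatment begins, the earlier grade is lost.

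**Working it through.** **Inputs from the protocol (section 4.4).** 15% versus 40%, two-sided alpha 0.05, 80% power, at least 61 per arm, 128 in total with 5% drop-out.

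**The plan's own figure.** For 15% versus 40% at 80% power, the pooled two-proportion formula gives 49 per arm, 57 with continuity correction, and Fisher's exact test needs 56. None gives 61. The stated number is on the large side: at 61 per arm, power is 0.88 by the pooled z-test and 0.84 by Fisher. The drop-out step does reproduce, since 122/0.95 = 128.4. The trial therefore has some reserve, and the question is how quickly dilution uses it up.

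**Assumption.** A share q of all patients, equal in both arms and independent of true toxicity, has a grade 3 or higher score not caused by (chemo)radiotherapy. The protocol gives no value for q. Suppose also that 15% and 40% exclude these events.

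**Formulas.** Observed rate = p + q(1 − p). With m the mean of the two observed rates and d their difference,

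power = Φ{ [d − 1.96·√(2m(1−m)/n)] / √[(p1(1−p1) + p2(1−p2))/n] }, n = 61.

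**Worked case, q = 0.** m = 0.275. The two standard errors are √(2 × 0.275 × 0.725/61) = 0.0809 and √((0.1275 + 0.24)/61) = 0.0776. Then (0.25 − 1.96 × 0.0809)/0.0776 = 1.18, and power = 0.881.

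**Worked case, q = 6%.** Rates are 0.15 + 0.06 × 0.85 = 0.201 and 0.40 + 0.06 × 0.60 = 0.436, so d = 0.235. The standard errors are 0.0844 and 0.0816. Then (0.235 − 1.96 × 0.0844)/0.0816 = 0.853, and power = 0.803.

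| q (assumed) | Observed rates | Difference (points) | Power, 61 per arm | n per arm for 80% (pooled) |
|---|---|---|---|---|
| 0 | 15.0% v 40.0% | 25.0 | 0.88 | 49 |
| 2% | 16.7% v 41.2% | 24.5 | 0.86 | 53 |
| 5% | 19.3% v 43.0% | 23.8 | 0.82 | 59 |
| 6% | 20.1% v 43.6% | 23.5 | 0.80 | 61 |
| 10% | 23.5% v 46.0% | 22.5 | 0.75 | 70 |
| 20% | 32.0% v 52.0% | 20.0 | 0.61 | 95 |

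Break-even with the planned 80% is near q = 6% at 61 per arm. If all 64 per arm are evaluable, as section 8.5 intends, power is 0.81 at 7% and 0.80 (0.796) at 8%, so break-even lies between 7% and 8%. By Fisher's test the reserve is smaller (0.84 at q = 0), so break-even comes sooner.

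**If 15% and 40% already include such events,** the observed rates stay as planned and power stays at 0.88. No further loss arises.

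**The case against.** An absolute grade at fixed times is a coherent endpoint, and the protocol contradicts itself nowhere on this point. The care providers who grade it may discount symptoms they regard as tumour-related. That is possible, but no rule tells them to, and the trial is not blinded. Informal attribution without a recorded earlier grade is a weak safeguard.

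The protocol also suggests that few patients enter with severe swallowing problems. Section 5.1 says enteral support is rarely needed before treatment, and section 11.4.1 says high-risk patients "more frequently experience swallowing problems than the study population". This stands for dysphagia and argues for a small q. It does not address pain or hoarseness.

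The calculation may overstate the loss. Surgery-only patients have no CTCAE score, so q must be averaged over everyone: if, say, 60% receive radiotherapy and 10% of those are affected, q is 0.60 × 0.10 = 6%, and power is still 0.80. If symptomatic patients are also those more prone to true toxicity, fewer events are added than the formula assumes. The planning rates may already contain such events; the cited studies are not at hand.

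A reader might infer that the result could not be read as an effect on treatment toxicity. That goes too far: under randomisation the false events dilute the difference, and the comparison between arms remains interpretable.

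A reader might also infer a sizeable problem from earlier surgery. The protocol gives little support. Section 4.3 excludes "Previous surgical or radiotherapeutic treatment of the neck", which leaves mainly surgery within the trial followed by radiotherapy. Section 5.1 allows that sequence, but its wording on "inability to start oral intake within 48 hours after surgery or no more than 50% of the recommended daily energy intake" is a trigger for postoperative nutritional care. It says nothing about symptoms 6 weeks into later radiotherapy.

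**Conclusion.** The point holds as a limited weakness in the endpoint. The protocol fixes an absolute grade, schedules no earlier CTCAE grade and gives no attribution rule, so severe tumour symptoms present at entry are counted as (chemo)radiotherapy toxicity. The expected consequence is dilution and lost power, not bias. Its size cannot be determined from the protocol. Under equal shares in both arms, independence from true toxicity, and planning rates that exclude such events, power at 61 per arm stays at or above the planned 80% up to about 6% affected, and is about 75% at 10% and 61% at 20%. If the planning rates already include these events, nothing further is lost. The case for acting rests on the low cost of the remedy and on the fact that the missing grade cannot be obtained later.

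**What to change.** In sections 8.1.3, 8.3 and 10.1:

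- Score the same eight CTCAE domains once at the enrolment visit, after consent and before randomisation.
- Keep the absolute grade of 3 or higher as the primary event.
- Prespecify the baseline CTCAE grade, or the baseline EORTC H&N35/C30 symptom scores already collected, as a covariate in the primary logistic model, whether or not the arms look unbalanced. State that these scores are taken before randomisation.
- Report new or worsened grade 3 or higher, relative to the pre-randomisation grade, as a sensitivity analysis. This needs the CTCAE form; the questionnaires alone cannot supply it.
- Do not define the primary event by a grade taken just before radiotherapy. That grade follows randomisation, prehabilitation and, in some patients, surgery, so the intervention may have changed it. If it is recorded, use it descriptively only.

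The cost is one short form per patient and one or two extra model terms. Covariate adjustment does not remove the pre-existing events from the outcome, and how much power it recovers cannot be calculated from the protocol.

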#### 8.1.2 Secondary study parameters/endpoints

Secondary outcome measures will be patient-reported quality of life outcome measures (i.e., the EAT-10, EORTC H&N35 and EORTC C30 questionnaires), recurrence and (disease-specific and overall) survival. Patients will be monitored for two years with intervals of at least three months. These intervals coincide with regular follow-up visits to the outpatient departments. The questionnaires will be fulfilled at baseline and at 3, 6, 12, 18 and 24 months after last treatment. Lastly, the EQ-5D-5L, *i*MCQ and *i*PCQ will be administered to be able to perform a cost-utility and cost-effectiveness evaluation. The EQ-5D-5L, *i*MCQ and *i*PCQ will be fulfilled in the first year of follow-up at baseline and at 3, 6 and 12 months after last treatment. The EORTC H&N35, EORTC C30, EQ-5D-5L questionnaires are part of our current standard practice, as well as the evaluation of recurrence and survival. The EAT-10, *i*MCQ and *i*PCQ are not part of our current standard practice.

#### 8.1.3 Other study parameters

Baseline characteristics include age, gender, smoking status, alcohol use, tumor site, tumor stage, (intended) type of treatment, length, weight (loss), skeletal muscle mass, number of dietetic consultations, dietary intake using 24-hour recall, nutritional status

using the MUST, Global Leadership Initiative on Malnutrition (GLIM)-criteria, Patient Generated Subjective Global Assessment Short Form (PG-SGA SF) score and bio-electrical impedance analyses (BIA)-measurements, physical status using grip strength and Timed Up and Go Test (TUG), and skeletal muscle mass. Dietary intake using 24-hour recall, GLIM-criteria, PG-SGA SF and BIA-measurements will not only be performed at baseline to assess nutritional status, but also at the end of the dietetic intervention (or, for the control group, just before the treatment starts), and three months after the final treatment.

The presence of (radiological) sarcopenia, or more specific skeletal muscle mass, will be measured at baseline and used within sub analysis. In patients with colorectal cancer, sarcopenia tended to be associated with treatment tolerance more often than other screening methods [24]. Sarcopenia is a progressive and generalized loss of muscle function and skeletal muscle mass. In its 2018 sarcopenia definition, the European Working Group on Sarcopenia in Older People 2 (EWGSOP2) requires a decrease in muscle function combined with a decrease in skeletal muscle mass [25]. The Sarcopenia Definitions and Outcomes Consortium, and the Special Interest Group on cachexia-anorexia in chronic wasting diseases of the European Society for Clinical Nutrition and Metabolism (ESPEN) support the use of both grip strength and skeletal muscle mass for defining sarcopenia [26, 27]. In oncology research, a (radiological) sarcopenia diagnosis is usually confirmed by the presence of low muscle quantity, which can be estimated using a variety of techniques, but usually CT is used for non-invasive assessment of muscle quantity. Skeletal muscle mass is most commonly assessed on a single CT slice at the abdominal level of L3, which has been shown to have excellent correlation with whole body skeletal muscle mass as measured using whole body MRI [28]. The cross-sectional skeletal muscle area (CSMA) at the level of L3 is then most commonly normalized for patients' squared height, to calculate the lumbar skeletal muscle index (LSMI). The latter is a surrogate marker for total body skeletal muscle mass [29]. In patients with head and neck cancer, abdominal imaging is not routinely performed, whereas imaging in the head and neck area is routinely performed. Therefore, measurement methods for skeletal muscle mass on a single axial slice at the cervical level of C3 have been developed [30-32]. The CT scans that are used for these measurements are part of our current standard diagnostic work-up. Pre-treatment CSMA at the level of C3 will be determined for each included patient using the methods described in previous papers written by members of our research team [30, 32]. The first slice when scrolling from caudal to cranial direction in the axial plane to show both transverse processes and

the entire vertebral arc will be selected. For CT, muscle tissue will be identified using Hounsfield Unit (HU) range settings from -29 to +150 HU, which is specific for muscle tissue [29]. In a semi-automatic procedure, densities within this range will be delineated. Manual adjustment is necessary to make sure large veins, arteries and lymph nodes are not included within the region of interest. Both sternocleidomastoid muscles and paravertebral muscles will be separately contoured. The CSMA will be calculated as the sum of these structures. The acquired CSMA at the level of C3 will be converted to CSMA at the level of L3 and subsequently corrected for patients' squared height to obtain the LSMI. Low LSMI will be defined as lower than 46.5 cm^2/m^2 for men and lower than 37.9 cm^2/m^2 for women [13]. Typically, 50 to 75% of patients with head and neck cancer have low skeletal muscle mass prior to the start of treatment [33-35]. Low skeletal muscle mass is a phenotypic criterion for malnutrition [36] and is associated with increased rates of intra- and postoperative complications, chemoradiotherapy toxicity and mortality in this patient population [33-35, 37, 38].

Grip strength and BIA-measurements are not part of our current standard practice.

